### Statistical analysis

We will perform statistical analysis on an intention-to-treat (ITT) basis. All data will be reported as mean ± standard deviation or numerical value (percentage). Non-normal distribution data will be presented as median (quartile interval, IQR). The chi-square test will be used to compare the categorical variables between the two groups. Continuous variables will be compared using sample *t* test for normally distributed data and Mann-Whitney *U* test for continuous variables of abnormal distribution. A non-corrected chi-square test will first compare the outcome variables of binary classification, and then the Cox proportional hazards model will be established to correct other confounding factors. The survival differences of the patients between the two groups will be compared using Log-Rank, and Kaplan-Meier survival curves will describe the results. Statistical analysis will be performed by using GraphPad Prism, and software R. *P* < 0.05 will be considered statistically significant.

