### Surveillance and follow-up

All participating hospitals use the same electronic case report form (eCRF) available at REDCap system to collect data of patients. All centers participating in the trial, ethics committee, and statisticians will have access to the system. Patients’ identity information is encrypted to prevent leakage. An independent data monitoring committee is responsible for summarizing and checking the data of each center. Moreover, if they have any questions, they can contact the co-investigators of each center to review or revise. Both the rivaroxaban group and the control group will be followed at 1, 3, 6, 12, 18, and 24 months after the operation. Once bleeding, thromboembolism, or other adverse events occur, patients need to report to the hospital immediately. The schedule of enrolment, interventions, and assessments is shown in Fig. 2.

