### Outcome measures

The primary outcome of the study is stent occlusion rate. The occlusion of stent will be confirmed by DUS and CTV. Stent occlusion is defined as DS > 50% for each modality with no procedure performed on the treated segment [19]. The secondary outcomes consist of quality of life scale survey results, all-cause mortality, anticoagulation-related mortality, and the proportion of participants with stent displacement/fracture, thrombosis, hemorrhage, and other vascular events. Quality of life will be assessed by MOS item short-form health survey scale (SF-36). SF-36 includes eight subscales: physical functioning (PF, ten items), role limitations due to physical health problems (RL-P, four items), bodily pain (BP, two items), general health (GH, five items), vitality (V, four items), social functioning (SF, two items), role limitations due to emotional problems (RL-E, three items), and mental health (MH, five items) [20]. Computed tomography (CT) will be used to detect stent displacement/fracture. Diagnosis of thrombosis will be based on color Doppler ultrasound and D-Dimer. Hemorrhage includes hemorrhagic stroke, gastrointestinal bleeding, hematuria, mucocutaneous hemorrhage, and another visceral bleeding. The diagnosis of hemorrhage will be based on clinical history, symptoms, laboratory examination, and imaging findings. For example, hematuria will be diagnosed according to the results of urinalysis. Moreover, the diagnosis of vascular events, including acute coronary syndrome, ischemic stroke, pulmonary embolism, transient ischemic stroke, and other parts of vascular embolism, will depend on CT/MRI.

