### Sample size calculation

According to Snyder et al., stent occlusion rate of thrombotic LIVCS was 20.2% [21]. For the noninferiority test of group design, 202 cases recruited in the study are enough under the power of 0.8, two-sided alpha level of 0.05, and the non-inferiority margin of 0.1. We will include 224 samples in the study, taking into account a dropout rate of 10%, 112 in the experimental group, and 112 in the control group.

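### If SF-36 is collected at baseline, the article's only rule for continuous variables (an unadjusted t test or Mann-Whitney test chosen by distribution) is valid but less precise than a baseline-adjusted analysis

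*Protocol article*

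**What the plan says.** The Statistical analysis section of the protocol article gives one rule for continuous data: "Continuous variables will be compared using sample *t* test for normally distributed data", and otherwise a "Mann-Whitney *U* test for continuous variables of abnormal distribution". It names no covariate or model for continuous data. Adjustment appears only in the next step, for binary outcomes, where "the Cox proportional hazards model will be established to correct other confounding factors".

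The Outcome measures section states that "Quality of life will be assessed by MOS item short-form health survey scale (SF-36" and lists eight subscales of two to ten items each. Every other outcome listed there is a rate, a mortality or a proportion.

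The Surveillance and follow-up section says that both groups "will be followed at 1, 3, 6, 12, 18, and 24 months after the operation". It does not say at which visits SF-36 is completed, or whether it is completed before treatment. For that the reader is referred elsewhere: "The schedule of enrolment, interventions, and assessments is shown in Fig. 2". That figure is not shown in the text available.

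**The concern.** The general rule is the only stated comparison that fits SF-36, so by default each subscale would be compared between arms without the patient's own starting score. Where such a score exists and predicts the later one, leaving it out makes the confidence interval wider than it needs to be and leaves any chance baseline imbalance in the estimate.

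The choice between the two tests also depends on the observed distribution. With eight subscales, some may pass a normality check and others fail it. Results for one questionnaire would then mix differences in means with shifts in rank, and a subscale could change test from one visit to the next. What is at stake is the precision and readability of the quality-of-life result.

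**Working it through.** **Inputs from the article.** The arms are 112 and 112, "taking into account a dropout rate of 10%, 112 in the experimental group, and 112 in the control group". This leaves 112 × 0.9 = 100.8, or about 101 per arm, which agrees with the stated 202 in total before dropout (202 / 2 = 101).

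**No figure to reproduce.** The article gives no SD, effect size, power or baseline correlation for SF-36. Its sample size concerns stent occlusion only.

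**Assumptions.** The correlation ρ between baseline and follow-up score is taken as 0.3, 0.5 and 0.7, with the same SD at both times. Two-sided alpha of 0.05 and 80% power serve as a yardstick for SF-36; the article makes no power claim for it.

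**Reading A: follow-up scores are compared.**
- Unadjusted detectable difference: (1.96 + 0.84) × √(2/101) = 2.80 × 0.1407 = 0.394 SD.
- ANCOVA multiplies the variance by 1 − ρ² and the standard error by √(1 − ρ²).
- The equivalent sample size per arm is 101 / (1 − ρ²).

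| ρ | Variance left | Variance cut | SE ratio | Detectable difference (SD) | Equivalent n per arm |
|---|---|---|---|---|---|
| 0.3 | 0.91 | 9% | 0.954 | 0.376 | 111 |
| 0.5 | 0.75 | 25% | 0.866 | 0.341 | 135 |
| 0.7 | 0.51 | 49% | 0.714 | 0.282 | 198 |

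For an assumed true difference of 0.4 SD, power is 0.81 unadjusted and 0.85, 0.91 and 0.98 with ANCOVA. At ρ = 0 there is no gain.

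**Reading B: change scores are compared.** The change-score variance is 2(1 − ρ) times that of a single score. The ratio of the ANCOVA standard error to the change-score standard error is therefore √(1 − ρ²) / √(2(1 − ρ)) = √((1 + ρ)/2):
- ρ = 0.3: √0.65 = 0.81
- ρ = 0.5: √0.75 = 0.87
- ρ = 0.7: √0.85 = 0.92

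Here the gain is largest at low correlation, the reverse of Reading A. Under either reading ANCOVA is, in large samples, at least as precise.

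**The switch.** A simulation used 4,000 runs with 101 per arm, scores bounded at 0 to 100 in steps of 5, and ρ = 0.5. A Shapiro test in each arm decided between *t* and Mann-Whitney.
- No true difference: rejection rates were 0.044 (switch), 0.046 (*t* test) and 0.046 (ANCOVA).
- True difference of 0.4 SD: power was 0.77, 0.79 and 0.88 respectively.

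With scores this coarse, normality was accepted in under 1% of runs, so in this setting the switch almost always meant Mann-Whitney. Type I error is not inflated. The switch costs about two points of power against a plain *t* test, and most of the gap to ANCOVA comes from the unused baseline score.

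**The case against.** The strongest objection is that the text does not establish that a baseline score exists. A reader might infer that the plan throws away baseline data it holds, but the article's text never says that SF-36 is taken before treatment, and the schedule that would settle this is not shown. If there is no baseline score, nothing is discarded. This objection stands, and the point is conditional for that reason.

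Second, the rule does not name SF-36, and the text does not say whether scores or changes are compared. That SF-36 falls under the rule is an inference, though the only one the outcome list allows. A *t* test on change does use the baseline, so the detectable differences in Reading A would not apply. This limits the size of the point but does not remove it, because ANCOVA is at least as precise as the change-score test too.

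Third, a reader might infer that the planned comparison is biased or invalid. It is not: randomisation makes the unadjusted test valid, and the simulation shows no excess of false positives.

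Fourth, the correlation is assumed. After stenting, and with follow-up to 24 months, it may be low; at 0.3 under Reading A the gain is slight.

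Finally, an analysis plan that is not shown may already specify a baseline-adjusted model. The choice of visit, the modelling of repeated measures and the reporting of intervals are matters that an article commonly leaves to that plan, and their absence is not counted here. The point concerns the method the article does state.

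**Conclusion.** The point holds in a limited, conditional form. The only rule stated for continuous variables covers SF-36 by default. It is valid, but if a baseline score is collected it is less precise than a baseline-adjusted analysis. The switch can also put subscales of one questionnaire on different scales of comparison.

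For follow-up scores, the standard error would fall by about 5%, 13% or 29% at ρ = 0.3, 0.5 or 0.7. Against change scores it would fall by about 19%, 13% or 8%. These sizes rest on the assumed correlation, equal SDs, 101 patients per arm and the existence of a baseline SF-36. The outcome is secondary, no power is claimed for it and the primary comparison is unaffected, so this is a minor efficiency improvement.

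**What to change.** For SF-36, replace the normality-based choice of test with ANCOVA on each subscale, with the baseline score as covariate. If the questionnaire is repeated over the visits, a mixed model with the same covariate serves. Report the adjusted mean difference with its 95% CI for every subscale, so that all eight are on the same footing.

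If baseline SF-36 is already in the schedule, this is a change of analysis wording only and costs nothing; R, which the article already names, can fit either model. If it is not, the adjustment needs one extra questionnaire at enrolment. The Trial status section says recruitment had not begun at the time of writing. Patients enrolled without a baseline questionnaire cannot be given one afterwards.

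### The trial is sized for non-inferiority with a 0.1 margin, but every planned test is a test of no difference at P < 0.05 and never uses the margin

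*Protocol article*

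**What the plan says.** Under Outcome measures: "The primary outcome of the study is stent occlusion rate". Each participant's stent is either occluded or not, so this is a binary outcome.

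Under Sample size calculation, the design is stated in these words: "For the noninferiority test of group design, 202 cases recruited in the study are enough". The error rates are set "under the power of 0.8, two-sided alpha level of 0.05", with "the non-inferiority margin of 0.1". The reference occlusion rate is 20.2%, and the total is raised to 224 (112 per arm) for 10% dropout.

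Under Statistical analysis, binary outcomes are handled thus: "A non-corrected chi-square test will first compare the outcome variables of binary classification". A Cox model then adjusts for confounders, and survival is compared by log-rank with Kaplan-Meier curves. All analyses are by intention to treat. The only decision criterion is that P < "0.05 will be considered statistically significant".

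Non-inferiority and the margin appear in the sample size section and nowhere else in the article.

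**The concern.** A non-inferiority trial must reject the hypothesis that the new treatment is worse by at least the margin. An ordinary chi-square, a log-rank test and a Cox test at P < 0.05 address a different hypothesis, that the arms do not differ. Failing to reject that hypothesis says nothing about whether a deficit of 10 points has been excluded.

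A team that follows the plan as written and sees P > 0.05 has two options. It can leave the sized question unanswered, or it can treat non-significance as evidence of non-inferiority. The second option is invalid and rewards a small trial, because fewer patients make a non-significant result more likely. At stake is the trial's main conclusion, namely whether rivaroxaban can replace warfarin plus nadroparin after iliac vein stenting.

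**Working it through.** **Inputs.** From Sample size calculation: control rate 0.202, margin 0.10, two-sided alpha 0.05, 202 evaluable patients (101 per arm) and 224 recruited (112 per arm). Two assumptions are added. The margin is read as an absolute risk difference, because its scale is not named. Where the arms are taken as equal, the rivaroxaban rate is set to 0.202, because no rate is stated for that arm.

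**What each stated analysis tests.**

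| Stated analysis | Null hypothesis | Uses the 0.1 margin? |
|---|---|---|
| Uncorrected chi-square | equal proportions | No |
| Log-rank | equal survival curves | No |
| Cox model at P < 0.05 | hazard ratio = 1 | No, and no margin is set on this scale |
| Needed for the sized hypothesis | difference ≥ 0.10 | Yes |

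**The two decision rules compared.** Let p_C and p_R be the observed proportions on control and rivaroxaban, n the number per arm, d = p_R − p_C, and p̄ the pooled proportion.

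- Chi-square: z = d / √[2p̄(1−p̄)/n], non-significant if |z| < 1.96.
- Margin rule: upper limit = d + 1.96·√[p_C(1−p_C)/n + p_R(1−p_R)/n], non-inferior if this is below 0.10.

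The probabilities below come from summing two independent binomial distributions over every possible pair of counts.

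| True rates (control, rivaroxaban) | n per arm | Chi-square non-significant | Margin rule met | Non-significant but margin rule not met |
|---|---|---|---|---|
| 20.2%, 30.2% | 101 | 62.7% | 2.6% | 60.2% |
| 20.2%, 30.2% | 112 | 59.2% | 2.6% | 56.6% |
| 20.2%, 20.2% | 101 | 94.9% | 42.9% | 54.5% |
| 20.2%, 20.2% | 112 | 95.0% | 46.5% | 51.0% |

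Using Newcombe's interval in place of the simple one changes none of the margin-rule figures by more than 0.1 percentage point.

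**Normal-approximation check at 112 per arm, rates 20.2% and 30.2%.** The pooled standard error is √(2 × 0.252 × 0.748 / 112) = 0.0580. The unpooled standard error is √[(0.202 × 0.798 + 0.302 × 0.698) / 112] = 0.0576. The probability of non-significance is about Φ[(1.96 × 0.0580 − 0.10) / 0.0576] = Φ(0.24) ≈ 0.59, in line with the exact 59.2%.

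**Worked example at 101 per arm.** Suppose there are 20 occlusions on control and 30 on rivaroxaban.

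- d = 10/101 = 0.099 and p̄ = 50/202 = 0.2475.
- z = 0.099 / 0.0607 = 1.63, so P = 0.10.
- The 95% interval is 0.099 ± 1.96 × 0.0603, or −1.9 to +21.7 points.

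The plan's criterion calls this not significant, yet the data are compatible with a deficit of more than twice the margin. Even 20 against 20 occlusions gives P = 1.0 with an upper limit of 1.96 × 0.0561 = 11.0 points, still above the margin.

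**The case against.** - **The plan never says that P > 0.05 will be read as non-inferiority.** This is true. The 59% and 63% figures are conditional on that reading and do not measure a stated rule. If the reading is refused, the plan has no analysis that answers the hypothesis it was sized on, which is also a defect.
- **The article is condensed, and interval methods and decision rules often sit in the analysis plan.** This would excuse silence. Here the article names the test for binary outcomes and the criterion, and stent occlusion is one of those outcomes. An analysis plan that used the margin would depart from the published text.
- **A significant result in favour of rivaroxaban would establish non-inferiority through superiority.** This is correct, so the planned tests are not wholly incapable of supporting the claim. But if both rates are 20.2%, that route opens in only about 2.5% of trials.
- **The sample size section may be the faulty side, since the objectives speak only of comparing efficacy and safety.** This is possible, and the sponsor must confirm which hypothesis is meant. The margin and the non-inferiority test are nevertheless stated explicitly, and no superiority hypothesis is. The two sections conflict either way.
- **With the margin rule in place the trial has low power.** This stands as a fact: about 43% at 101 per arm and 46% at 112 if both rates are 20.2%, against the stated 80%. It is a separate sample-size problem that exists already and is not created by the correct analysis.

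**Conclusion.** The concern holds and must be fixed. The stated analysis does not match the stated hypothesis, and it concerns the primary outcome. With similar arms, none of the planned tests can establish non-inferiority. If non-significance were taken as a substitute, a drug worse by the full 10 points would pass about 59% of the time (112 per arm) or 63% (101 per arm), against 2.6% under a 95% confidence interval rule.

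These sizes rest on a control rate of 20.2%, an absolute-difference margin and complete outcome data at the stated arm sizes. The mismatch itself rests on none of these, nor on whether 202 is the right sample size.

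**What to change.** In Statistical analysis, replace the general chi-square sentence, for the primary outcome, with the following:

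1. The primary analysis is the difference in stent occlusion proportion, rivaroxaban minus control, with a two-sided 95% confidence interval. Name one method in advance, such as Newcombe or Farrington-Manning.
2. Non-inferiority is declared only if the upper limit is below 0.10, stated as an absolute difference. The 95% interval corresponds to the two-sided 0.05 already chosen in the sample size section.
3. The chi-square test of superiority is carried out only after non-inferiority has been shown.
4. P > 0.05 will not be read as evidence of non-inferiority.
5. The Cox and log-rank analyses are supportive, because no margin is set on the hazard-ratio scale.

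The cost is protocol and analysis-plan wording, with no extra data. The article's Trial status section says recruitment had not begun, so at that stage the change could be made before any outcome was seen. The sponsor should review the sample size separately, because this change does not repair the power shortfall noted above.

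### The trial is sized for non-inferiority with a 0.1 margin on the occlusion rate, but no analysis the article states evaluates that margin, and its only adjusted one is a Cox hazard ratio

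*Protocol article*

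**What the plan says.** Outcome measures: "The primary outcome of the study is stent occlusion rate", a yes/no outcome per patient based on a stenosis threshold.

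Sample size calculation: the design is a non-inferiority test with an assumed occlusion rate of 20.2% and "the non-inferiority margin of 0.1". The section adds that "202 cases recruited in the study are enough under the power of 0.8, two-sided alpha level of 0.05", and reaches 224 after allowing for dropout. The scale of the margin is not stated. On an occlusion rate it reads as an absolute difference of 10 percentage points; as an upper limit for a hazard or odds ratio, 0.1 would make no sense.

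Statistical analysis: the analysis is by intention to treat. An uncorrected chi-square test comes first for the binary outcomes. The adjusted step follows it: "then the Cox proportional hazards model will be established to correct other confounding factors". Survival is compared by log-rank and shown by Kaplan-Meier curves, and P < 0.05 counts as significant. The section does not mention the margin, a confidence limit or non-inferiority.

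Surveillance and follow-up: both groups "will be followed at 1, 3, 6, 12, 18, and 24 months after the operation". Neither the outcome section nor the sample size section ties the occlusion rate to one of these times.

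**The concern.** A non-inferiority claim needs a confidence limit for the treatment effect, set against the margin on the margin's own scale. The article supplies the margin in one section and, in the next, only tests of no difference plus a hazard ratio.

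Two things follow. First, the chi-square and log-rank tests answer whether the arms differ, so a non-significant result could be mistaken for non-inferiority. Second, the adjusted result comes on a scale for which no margin exists. Turning 0.1 into a hazard-ratio limit needs a control rate and a time point. If these are chosen after the data are seen, the same hazard ratio can be made to pass or fail.

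**Working it through.** **Inputs.** From Sample size calculation: rate 20.2%, margin 0.1, power 0.8, two-sided alpha 0.05 (one-sided 0.025 for non-inferiority), 202 evaluable, 224 randomised 1:1. Assumptions made here: the same true rate in both arms (no separate rivaroxaban rate is given) and, for the conversions, proportional hazards.

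**1. The plan's own figure.** n per arm = 2p(1−p)(1.960 + 0.842)² / margin² = 2 × 0.202 × 0.798 × 7.849 / 0.01 = 253.04, so 254 per arm and 508 in total. The stated 202 is not reproduced. That is a separate matter from this point, but it affects what the right analysis could show (step 4).

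**2. Hazard ratio equivalent to the margin.** With control rate pc, HR = ln(1 − pc − 0.10) / ln(1 − pc).

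| Control rate | Calculation | HR equal to a 10-point difference |
|---|---|---|
| 10% | ln 0.800 / ln 0.900 = −0.2231 / −0.1054 | 2.12 |
| 20.2% | ln 0.698 / ln 0.798 = −0.3595 / −0.2256 | 1.59 |
| 30% | ln 0.600 / ln 0.700 = −0.5108 / −0.3567 | 1.43 |

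In the other direction, the risk difference implied by HR 1.593 is 1 − (1 − pc)^1.593 − pc. This is 5.5 points at a control rate of 10%, 10.0 at 20.2% and 13.4 at 30%. A single hazard-ratio limit therefore does not stand for the 0.1 margin.

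**3. Events.** Expected occlusions are 202 × 0.202 = 40.8, or 224 × 0.202 = 45.2. If 1.59 were adopted as the limit, the events needed at one-sided 0.025 and 80% power are 4 × 7.849 / (ln 1.593)² = 31.396 / 0.2170 = 144.7, so 145. Power with the expected events is Φ(√40.8 × 0.4658/2 − 1.960) = 32%, or 35% with 45.2 events.

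**4. What the chi-square test says about the margin.**

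- *Identical observed rates of 20.2%, 101 per arm.* The chi-square statistic is 0 and P = 1. The standard error of the difference is √(2 × 0.202 × 0.798 / 101) = 0.0565, so the 95% interval is ±1.96 × 0.0565 = ±0.111. The upper limit is above 0.10, so non-inferiority is not shown. With 112 per arm it is ±0.105, with the same conclusion.
- *Rivaroxaban observed worse by exactly the margin, 30.2% against 20.2%.* The pooled rate is 0.252. With 101 per arm, SE = √(2 × 0.252 × 0.748 / 101) = 0.0611, z = 0.10 / 0.0611 = 1.64 and P = 0.10. With 112 per arm, z = 1.72 and P = 0.085. The test reports no significant difference when the point estimate itself sits on the margin.

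The P < 0.05 rule gives no answer about non-inferiority in either case.

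**The case against.** The strongest reply is that this is a condensed article. A full protocol or analysis plan may define the margin test, the covariates and which result governs, and an adjusted model after an unadjusted test is common practice. Much of that stands, and it limits the point in five ways.

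- A reader might infer that Cox is the primary or confirmatory analysis. The text does not say so: it is a second step for binary outcomes in general.
- A reader might infer that covariates will be picked from observed imbalance, because they are called confounders in a randomised trial. The wording is unfortunate, but a covariate list commonly sits in the analysis plan, so its absence here is no error.
- It might seem that hospital is left out of the model. No covariate is named, so this cannot be known.
- It might seem that event times are heavily tied because of the six visits. The visit times are given, but the assessment schedule is in a figure not shown, and patients must also report adverse events at once.
- It is too strong to say that a hazard ratio can never be compared with the margin. A conversion exists, and an adjusted risk difference can be derived from a Cox model. Both need a control rate and a time point, and the article does not state a conversion.

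What the reply does not remove is the conflict within the article. It does more than stay silent: it lists its tests and gives a decision rule, and none of them fits the non-inferiority hypothesis in the preceding section.

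**Conclusion.** The point holds in this form: as published, the stated analyses do not test the non-inferiority hypothesis that sized the trial, and the only adjusted analysis is on a scale that cannot be set directly against the margin. The hazard-ratio equivalent of 0.1 runs from 2.12 to 1.43 as the control rate goes from 10% to 30%, with 1.59 only at the planning rate.

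This rests on reading 0.1 as an absolute difference, which is the only sensible reading for a rate. The conversions also assume proportional hazards; without them, the link between the two scales is looser still. The change should be made before the data are analysed. If an unseen analysis plan already contains a margin-based test, what remains is to bring the article's section into line with it.

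A correct analysis will not rescue the sample size. At equal true rates of 20.2%, power against the 0.1 margin is Φ(0.10/0.0565 − 1.960), about 43% with 101 per arm, and about 46% with 112.

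**What to change.** In Statistical analysis, name the non-inferiority analysis of the primary outcome: the risk difference in stent occlusion, rivaroxaban minus control, at one stated time point, with a two-sided 95% confidence interval. Conclude non-inferiority only if the upper limit is below 0.10. State in Sample size calculation that the margin is an absolute difference.

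Do any adjustment on the same scale, by a logistic model standardised to a risk difference or by a Mantel-Haenszel difference, against the same 0.10. Prespecify only a few prognostic covariates, because about 41 events are expected. If hospital is used, 9 sites mean 8 indicators; with treatment and one or two further covariates that is 10 or 11 parameters, or about 4 events each (40.8/10 = 4.1; 40.8/11 = 3.7). Small sites would then need pooling, or hospital could be the stratifier in the Mantel-Haenszel difference. Label the Cox, log-rank and Kaplan-Meier analyses as supportive, and replace the reference to confounding with prespecified prognostic covariates.

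The cost is a wording change and standard code in R, which the article already names. It needs no extra patients or visits. The team must commit to one time point and, if hospital is used, to a pooling rule.
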